### Antibiotics

1.5g of cefuroxime sodium will be given 30 min preoperatively and every 12 h for 6 times by intravenous drip after the TKA

### Pain management and rehabilitation

The strategies to alleviate pain for all patients will be the same. Intravenous or oral NSAIDs combined with patients-controlled intravenous analgesia (PCIA) will be used after TKA for analgesia. Daily function training (active range of motion training, strength training, and walking training) will be followed out under the supervision and assistance of a physiotherapist.

### Venous thromboembolism prophylaxis

All patients will receive the same routine chemical thromboprophylaxis after operation. Patients will receive 10 mg Rivaroxaban (Xarelto, Bayer, Germany) 12 h postoperatively, repeating at 24-h intervals for 14 days.

### Primary outcomes

#### Perioperative blood loss

The patient’s blood volume (PBV) and perioperative blood loss are calculated according to Nadle et al. [28] and Gross formula [29]:

The patient’s blood volume (PBV) [28] = k1 × height (m) + k2 × weight (kg) + k3 (male: k1 = 0.3669, k2 = 0.03219, k3 = 0.6041; female: k1 = 0.3561, k2 = 0.03308, k3 = 0.1833 for women).

The total blood loss (TBL) [29] = PBV × (Hct_pre_ − Hct_post_)/ Hct_ave_ (Hct_pre_ = preoperative hematocrit level. Hct_post_ = the lowest postoperative hematocrit level during hospitalization. Hct_ave_ = the average of the Hct_pre_ and Hct_post_).

The intraoperative blood loss (IBL) [30] = (the weight of the gauze pads and compresses with blood – the dry weight of the gauze pads and compresses) + (the volume collected by the aspirators – the volume used to wash the surgical area).

The hidden blood loss (HBL) [31] = TBL – measured blood loss (measured blood loss mainly included IBL and the volume of drainage).

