**Methods/design:**

The study will be a double-blind randomized controlled trial with two parallel groups of RA patients. Group A will be given 100 ml normal saline twice daily starting from 3 days before the operation, Group B will be given TXA 1.5 g twice daily starting from 3 days before the operation. All patients will be given TXA 1.5 g 30 min before the operation. The primary outcomes will be evaluated with total blood loss and hidden blood loss. Other outcome measurements such as, fibrinolysis parameters, inflammatory factors, visual analogue scale for post-operative pain, analgesia usage, coagulation parameters, transfusion, the length of stay (LOS), total hospitalization costs, the incidence of thromboembolic events and other complications will be recorded and compared. Recruitment is scheduled to begin on 1 August 2020, and the study will continue until 31 May 2021.

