### Sample size calculation

Sample size was estimated based on a large database generated from a prospective multicenter study sponsored by the Chinese Health Ministry (project number 201302007) using PASS 2011 (NCSS, LLC. Kaysville, Utah, USA) software. According to the database, the TBL was 730.96 ± 262.85 mL, with a single dose of TXA before TKA in RA patients. To detect a difference of 200 mL of primary end point, with a power of 0.90 and the significance level of 0.05, 31 patients per arm will be needed. Considering a dropout rate of 20%, we decided to involve 39 patients in each arm.

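### The blood-volume formula prints height to the first power where the cited formula uses height cubed; applied as printed, it understates TBL and HBL in both arms

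*Protocol article*

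**What the plan says.** The abstract names the two primary outcomes: "The primary outcomes will be evaluated with total blood loss and hidden blood loss". The Perioperative blood loss section defines both through the patient's blood volume.

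- **PBV** (reference 28) is "k1 × height (m) + k2 × weight (kg) + k3", with constants "male: k1 = 0.3669, k2 = 0.03219, k3 = 0.6041" and "female: k1 = 0.3561, k2 = 0.03308, k3 = 0.1833". No exponent is printed on height.
- **TBL** (reference 29) is "PBV × (Hct_pre_ − Hct_post_)/ Hct_ave", the last term being the mean of the two hematocrits. TBL is therefore directly proportional to PBV.
- **HBL** (reference 31) is TBL less measured loss, where "measured blood loss mainly included IBL and the volume of drainage".

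The section presents these as published formulas ("perioperative blood loss are calculated according to" the cited sources) and announces no modification. The Sample size calculation section plans on existing data: "According to the database, the TBL was 730.96 ± 262.85 mL", with a target difference of 200 mL.

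**The concern.** The article names a published formula and prints its sex-specific constants, but the height term lacks the cube that belongs to them. With height to the first power, the volume hardly responds to height and comes out very low per kilogram.

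PBV multiplies the first primary outcome and feeds the second. Anyone who programs the printed line obtains TBL, HBL and between-group differences that are too small in mL. Those results could not be set against the planning mean or the 200 mL target if these came from the cubed form.

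**Working it through.** The article states no blood volume, so there is no figure of its own to reproduce. The check evaluates the printed constants with height to the first power and with height cubed, then carries the result through the printed TBL and HBL definitions. Heights, weights and measured losses are assumptions; constants, planning mean and target difference are the article's.

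**1. Direction.** Cubed minus printed PBV is k1 × (h³ − h). This is positive for every height above 1 m, so the printed form is too low for all plausible adults.

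**2. Single patients.**

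- Woman, 1.60 m, 60 kg, printed: 0.3561 × 1.60 + 0.03308 × 60 + 0.1833 = 0.5698 + 1.9848 + 0.1833 = 2.738 L (46 mL/kg).
- Same woman, cubed: 0.3561 × 4.096 + 1.9848 + 0.1833 = 3.627 L (60 mL/kg). Ratio 0.755, shortfall 24.5%.
- Woman, 1.58 m, 58 kg: 2.665 L against 3.507 L. Ratio 0.760, shortfall 24.0%.
- Man, 1.70 m, 65 kg, printed: 0.3669 × 1.70 + 0.03219 × 65 + 0.6041 = 3.320 L. Cubed: 0.3669 × 4.913 + 2.0924 + 0.6041 = 4.499 L. Ratio 0.738, shortfall 26.2%.

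**3. Influence of height.** For a woman at fixed weight, going from 1.50 m to 1.75 m adds 0.3561 × 0.25 = 0.09 L as printed, and 0.3561 × (5.3594 − 3.3750) = 0.71 L cubed.

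**4. Range over 1.50-1.75 m and 50-75 kg.** The extremes lie at the corners.

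| Build | Printed (L) | Cubed (L) | Ratio |
|---|---|---|---|
| Woman, 1.75 m, 50 kg | 2.460 | 3.746 | 0.657 |
| Man, 1.75 m, 50 kg | 2.856 | 4.180 | 0.683 |
| Woman, 1.50 m, 75 kg | 3.198 | 3.866 | 0.827 |
| Man, 1.50 m, 75 kg | 3.569 | 4.257 | 0.838 |

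The ratio runs from 0.66 to 0.84, a shortfall of 16-34% that depends on build.

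**5. Carried to TBL.** Suppose the planning figures used the cube. With the three ratios in step 2, a mean of 730.96 mL would read 730.96 × 0.738 = 539 mL to 730.96 × 0.760 = 555 mL, and a difference of 200 mL would read 148 to 152 mL. Under a common factor the SD shrinks too. With ratio 0.755, 262.85 mL becomes 198.4 mL and 200 mL becomes 151.0 mL, so difference/SD stays at 0.761.

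**6. Carried to HBL.** With TBL ratio r and measured loss M, the relative shortfall in HBL is (1 − r) × TBL / (TBL − M). Taking r = 0.760 (the 1.58 m, 58 kg woman), the numerator is 730.96 − 555.45 = 175.5 mL.

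- M = 200 mL: 175.5 / 530.96 = 33%.
- M = 300 mL: 175.5 / 430.96 = 41%.

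The article gives no measured loss, so these two values only illustrate the size.

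**The case against.** **The cube is not in the article.** This is true: no section prints an exponent, and reference 28 is not at hand. Calling 46 mL/kg implausible also uses an outside norm. The article's own planning mean does not separate the two forms. For the 1.60 m, 60 kg woman with an assumed preoperative hematocrit of 0.38, a TBL of 730.96 mL implies a lowest value of 0.29 as printed and 0.31 with the cube, both possible. What remains is that the formula is identified by its citation and its constants, and that the printed version makes a height-and-weight formula almost insensitive to height. That is more than recall of a reference, but the source should still be opened.

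**A superscript may have been lost in typesetting or conversion.** This cannot be excluded, as the text contains no other superscript to test it against. It is unlikely: the subscripts in the same section survive, and no stray 3 follows the height term.

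**Harm arises only if the printed line is programmed.** This stands. The article says that the calculation follows the cited source, and nothing shows that the analysis program used the first power.

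**The comparison is still randomized.** This also stands. A reader might infer a biased treatment comparison or lost power. Neither follows for TBL, because both arms use the same expression and mean and SD shrink nearly together. Patient-to-patient variation in the ratio makes this approximate. The same argument does not settle the HBL test, where only one of two components is scaled; without measured losses, no size can be given.

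**Conclusion.** The point holds as an error in a stated formula for the primary outcomes. Applied as printed, PBV and TBL are about 24-26% too low for average builds and 16-34% too low over 1.50-1.75 m and 50-75 kg. A reader might infer that every volume is a quarter too low; that fits average builds only, and because the shortfall varies with build, a single correction factor will not do. HBL is understated by proportionally more, about 33-41% on the assumed measured loss of 200-300 mL.

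The damage is to the reported mL values of TBL, HBL and their differences, and to comparability with the planning mean and the 200 mL target.

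Three assumptions carry this: that reference 28 uses the cube, as its constants indicate; that the printed form is the one applied; and, for comparability, that the planning database used the cube. The unstated conversion from litres to mL is a detail that an article may omit and is not part of the point.

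**What to change.** 1. Check the source file and reference 28 for the exponent.
2. Print PBV (L) = k1 × height(m)³ + k2 × weight(kg) + k3, with the constants unchanged.
3. Confirm that the analysis program and the planning database use this form.
4. Where either used the first power, recompute PBV, TBL and HBL patient by patient from height, weight, hematocrit and measured loss.

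The cost is one character in the text and a short code check. Recomputation, if needed, uses only quantities that the outcome definitions already require.

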## Background

As the one of the most common inflammatory arthritis affecting about 1% of world population [1, 2], rheumatoid arthritis (RA) is associated with an increasing socioeconomic impact and often affects the diarthrodial joints, including knee joint [3, 4]. Total knee arthroplasty (TKA) is considered one of the most effective orthopedic health care interventions for patients with rheumatoid arthritis (RA) [5–8], and RA patients achieve better satisfaction after TKA compared to patients with osteoarthritis (OA) [8]. However, fibrinolysis stimulated by surgical trauma could lead to significant blood loss [9, 10], and RA patients undergoing this procedure tend to have a higher risk of requiring transfusion than OA patients, owing to preoperative anemia, lower average weight, great bone mass loss, complete synovectomy and extensive soft tissue separation [11, 12]. Blood transfusion is often associated with infectious or noninfectious complications [13], and can prolonged hospital stays, delay recovery and increase medical expenses [14]. Therefore, decreasing blood loss, which can subsequently reduce the requirement for transfusion, is extremely important for patient to improve the quality of life.

As an antifibrinolytic agent, the hemostatic effect of tranexamic acid (TXA) has been proven in TKA [9, 10, 15]. However, in view of the fact that almost 97% of TKAs are performed for OA [16], current published studies in terms of the efficacy of TXA were mainly based on the experience in OA patients [9, 17–20], and there still exists a paucity of evidence with regard to the efficacy of TXA in RA patients. Unlike OA, RA has its own features in the aspects of pathogenesis, prognosis, and medical management [5]. It has been reported that RA patients had higher preoperative D-dimer value than OA patients [21]. Therefore, TXA is theoretically more suitable for RA patients compared to OA patients, and a specially designed TXA scheme for RA patients with TKA is urgently needed.

The most common preoperative protocol of TXA in TKA is to administer one single dose prior to skin incision [9, 22–24], which might seem to be insufficient to inhibit fibrinolysis in RA patients. Therefore, we plan to conduct a randomized clinical trial to compare the effects of preemptive antifibrinolysis of single-dose and repeat-dose TXA in RA patients undergoing TKA.

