**Outcome assessment**									
TBL				●	●	●			
IBL			●						
HBL				●	●	●			
Hemoglobin level	●	●		●	●	●		●	
Fibrinolysis parameters	●	●		●	●	●		●	
Inflammatory markers	●	●		●	●	●		●	
Coagulation parameters	●	●		●	●	●		●	
Pain level	●	●		●	●	●		●	
Analgesia usage				●	●	●			
Knee range of motion	●	●		●	●	●		●	●
LOS						●			
Hospitalization costs						●			
DVT						●		●	●
PE						●		●	●
Adverse events				●	●	●	●	●	●

Pre-D3, 3 days before surgery; Pre-D1, 1 day before surgery; OP, operative; TBL, total blood loss; IBL, intraoperative blood loss; HBL, hidden blood loss; LOS, length of stay; DVP, deep vein thrombosis; PE, pulmonary embolism; D1, the 1st day after surgery; D2, the 2nd day after surgery; D3, the 3rd day after surgery; DOD, the day of discharge; D14, the 14th day after surgery; D90, the 90th day after surgery

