#### Transfusion and knee function

Transfusion will be carefully recorded during hospitalization and follow-up period. The criterion of blood transfusion in our medical institution will be in accordance with the guidelines of the National Ministry of Health [9]: (1) the hemoglobin (Hb) level is equal to or less than 70 g/L; (2) the Hb level is between 70 g/L and 100 g/L, with intolerable symptom of anemia (dizziness, tachycardia, tachypnea, or decreased exercise tolerance).

The knee range of motion will be measured preoperatively and 1, 2, 3, 14 and 90 days after TKA, and the knee angle will be measured by goniometer.

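### Total and hidden blood loss are computed net of transfused red cells, and the hematocrit window in the formula does not match Table 1

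*Protocol article*

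**What the plan says.** The abstract of the protocol article names the outcomes: "The primary outcomes will be evaluated with total blood loss and hidden blood loss". The section Perioperative blood loss writes TBL out in full as "PBV × (Hct_pre_ − Hct_post_)/ Hct_ave", where the postoperative hematocrit is "the lowest postoperative hematocrit level during hospitalization". HBL is then "TBL – measured blood loss (measured blood loss mainly included IBL and the volume of drainage").

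Transfusion is expected. The Background says that "RA patients undergoing this procedure tend to have a higher risk of requiring transfusion than OA patients". The section Transfusion and knee function gives the trigger, either "the hemoglobin (Hb) level is equal to or less than 70 g/L" or a level between 70 and 100 g/L with symptoms, and adds: "Transfusion will be carefully recorded during hospitalization and follow-up period". Transfusion is a secondary outcome there and enters neither primary outcome.

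Table 1 marks TBL and HBL on D1, D2 and D3 only. Hemoglobin is marked on Pre-D3, Pre-D1, D1 to D3 and D14; hematocrit has no row of its own. The day of discharge is a separate column ("D3, the 3rd day after surgery; DOD, the day of discharge"), and length of stay is a secondary outcome.

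**The concern.** A fall in hematocrit measures red cells lost minus red cells given back. Where red cells are given during surgery, or after it but before the draw that becomes the postoperative value, that draw is higher than it would have been and the replaced loss drops out of TBL. Transfusion is triggered by blood loss, so the error falls on the patients who bled most. If repeat dosing works as the Discussion supposes, more of those patients are in Group A, and the treatment difference is pulled toward zero.

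HBL is exposed in the same way. Intraoperative loss and drainage are counted gross and subtracted from a TBL that is net of transfusion. The full error therefore lands on a smaller quantity, which could even turn negative in a transfused patient.

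Two further parts of the definition are loose. The formula's search window (the whole stay) differs from Table 1's (D1 to D3). And the preoperative hematocrit is not tied to either of the two preoperative blood draws.

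**Working it through.** **1. The plan's own figure.** Inputs from Sample size calculation: SD 262.85 mL, difference 200 mL, power 0.90, significance level 0.05, dropout 20%. A t-test calculation gives 31 per arm if the test is one-sided (power 0.906; 0.898 at 30). A two-sided test needs 38 (power 0.906). Dropout: 31/(1 − 0.20) = 38.75, so 39. The stated 31 and 39 reproduce on the one-sided reading. Sidedness is a separate matter, so both readings appear below.

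**2. One patient, for illustration.** Assume a blood volume of 4,000 mL and a preoperative hematocrit of 0.36.
- Lowest value 0.30: 4,000 × 0.06/0.33 = 727 mL.
- Same bleeding, but red cells given before the draw lift it to 0.32: 4,000 × 0.04/0.34 = 471 mL.

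The formula misses 727 − 471 = 256 mL. If TBL is low by *e* mL, then HBL = (TBL − *e*) − measured loss, so HBL is also low by *e*.

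**3. Effect on the group difference.** Let p_A and p_B be the shares of patients with missed volume and *m* the mean volume missed in each, taken as equal in both arms. Then:

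observed difference = 200 − (p_A − p_B) × *m*

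The documents give neither p nor *m*. Shrinkage in mL over an assumed range:

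| Transfusion gap, A minus B | 100 mL missed | 200 mL missed | 400 mL missed |
|---|---|---|---|
| 0 points | 0 | 0 | 0 |
| 5 points | 5 | 10 | 20 |
| 10 points | 10 | 20 | 40 |
| 15 points | 15 | 30 | 60 |
| 20 points | 20 | 40 | 80 |

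Power at 31 per arm (normal approximation), conditional on these assumptions:

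| Observed difference | One-sided | Two-sided |
|---|---|---|
| 200 mL | 0.912 | 0.850 |
| 195 mL | 0.899 | 0.832 |
| 180 mL | 0.853 | 0.769 |
| 160 mL | 0.774 | 0.669 |
| 120 mL | 0.561 | 0.435 |

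**4. The search window.** The minimum over a longer period is never higher than the minimum over a shorter one. Extending the search from D1–D3 to the whole stay therefore leaves the postoperative hematocrit unchanged or lowers it, and TBL stays the same or rises. If one arm stays longer or is sampled more often, it has more chances of a low value.

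**5. The preoperative draw.** With the same assumed 4,000 mL and a lowest value of 0.30, a preoperative value of 0.36 gives 727 mL, and 0.35 gives 4,000 × 0.05/0.325 = 615 mL. One hematocrit point between Pre-D3 and Pre-D1 moves TBL by 112 mL.

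**The case against.** The strongest reply is that taking the lowest hematocrit already protects the measure. A postoperative transfusion is prompted by a low hemoglobin, and the sample that prompts it is eligible as the postoperative value. Loss up to that draw is then counted. This stands: understatement is not automatic, and it need not equal the volume transfused. What remains exposed is blood given during surgery or before the qualifying draw, and later bleeding that transfused cells mask.

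A second reply is that both arms receive 1.5 g of TXA before surgery, so the transfusion gap may be small, and the article reports no rate. This also stands, and it limits what can be said about size. It is no answer that an article condenses the full protocol, because the formula is written out in full and defines a primary outcome.

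Three stronger readings are tempting but unsupported:
- A reader might infer that the open-ended window also understates loss. Its direction is the opposite. If Group A stays longer, the window would widen the difference and work against the transfusion effect.
- A reader might infer that the comparison is shown to be biased toward no difference. The two effects have not been netted, and the documents do not allow it.
- A reader might infer a large loss of power. That needs the far corner of the assumed range, with a wide transfusion gap and a large missed volume in every transfused patient.

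**Conclusion.** The point holds in a limited form. As written, TBL measures loss net of replacement. It is too low in any patient transfused before the draw that supplies the postoperative hematocrit, and HBL is too low by the same number of mL. The effect on the group comparison is conditional. If Group A is transfused more, the difference shrinks by the transfusion gap times the missed volume: 5 to 80 mL of the 200 mL target under the assumed 5 to 20 points and 100 to 400 mL. If transfusion and missed volume are equal between arms, the mean difference is unaffected, although individual values remain wrong. No single corrected figure can be derived from the documents.

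Separately, the formula's window and Table 1 disagree, and the preoperative draw is not named. These are faults of definition whose net direction is unknown. The case for correction rests on the validity of both primary outcomes, not on a demonstrated size of bias.

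**What to change.** - Add to TBL the volume of red cells transfused from the start of surgery to the draw that gives the postoperative hematocrit, with a stated conversion to whole-blood equivalent. Use that TBL in HBL.
- Take the postoperative hematocrit as the lowest of the scheduled D1, D2 and D3 draws in every patient, so that the outcome definition and Table 1 agree.
- Name one preoperative draw for both arms. Pre-D3 is the day of randomization; Pre-D1 falls after the study infusions have begun. The documents do not settle the choice, but it must be made before unblinding.
- As a sensitivity analysis, compute TBL from the D3 hematocrit plus all red cells transfused up to D3 (same conversion). This captures loss after the lowest value, which the main definition still misses.

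The cost is small but goes beyond wording. The article says that transfusion is recorded, but not that the volume and the time relative to each draw are. Both need a field on the case report form. No extra blood draw is needed, provided hematocrit is reported with the scheduled hemoglobin.

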### Secondary outcomes

#### Fibrinolysis parameters, inflammatory markers and coagulation parameters

Fibrinolysis parameters [fibrin(−ogen) degradation products (FDP), D-dimer], inflammatory markers [erythrocyte sedimentation rate (ESR), C-reactive protein (CRP), interleukin-6 (IL-6)] and coagulation parameters [activated partial thromboplastin time (APTT), prothrombin time (PT) and thrombelastography (TEG)] will be tested 1 and 3 days before surgery and 1, 2, 3 and 14 days after surgery. All measurements will be performed by the Department of Clinical Laboratory of The First Affiliated Hospital of Chongqing Medical University.

#### Post-operative pain score and analgesia usage

Pain level at rest (rest in bed at least for 30 min before test) and during activity (from sitting to standing position) will be assessed using a visual analogue scale (0 means no pain, 10 means severe pain imaginable) and will be conducted 1 and 3 days before surgery and 1, 2, 3 and 14 days after surgery, and the analgesia usage will be carefully recorded.

#### Transfusion and knee function

Transfusion will be carefully recorded during hospitalization and follow-up period. The criterion of blood transfusion in our medical institution will be in accordance with the guidelines of the National Ministry of Health [9]: (1) the hemoglobin (Hb) level is equal to or less than 70 g/L; (2) the Hb level is between 70 g/L and 100 g/L, with intolerable symptom of anemia (dizziness, tachycardia, tachypnea, or decreased exercise tolerance).

The knee range of motion will be measured preoperatively and 1, 2, 3, 14 and 90 days after TKA, and the knee angle will be measured by goniometer.

